### 20.2 Analysis

#### 20.2.1 Quantitative analysis

Formal review of recruitment rates will take place at month 15. Criteria for continuation are: recruitment of at least (minimum) 25 patients, SIPC commenced within 3 weeks of randomisation in at least 80% of patients in the SIPC arm, Specialist palliative care received within 11 weeks of randomisation in less than 10% of patients in the control arm. Recruitment rates will continue to be monitored throughout the trial. The analysis will focus on assessing the criteria for continuation and any modifications needed. Analysis will be undertaken according to CONSORT guidelines by our Clinical Trials Unit with the trial statistician being blind to treatment assignment. A flow chart will present the follow-up rate for each group, with the reason for non-completion of the primary outcome. In view of the short duration of the trial no interim analysis is planned.

Attrition will be classified according to the MORECARE classification as to whether it is Attrition Due to Death (ADD), Attrition Due to Illness (ADI) or Attrition at Random (AaR) [79]. We will explore and report reasons for missing data, and any factors associated with missing data, in particular differences between study arms. As data are more likely to be missing when patients are ill, we expect missing data to be missing not at random.

Analysis of primary outcome (IPOS Neuro-S8): The primary analysis will be on an intention-to-treat (ITT) basis using generalised linear mixed model with centre as a fixed effect, adjusting for baseline score of IPOS Neuro-S8 and for variables from the baseline assessment for which treatment-group imbalance is found. The intervention effects and 95% confidence intervals will be estimated. We will test for intervention by center interaction. The missing data will be explored and dealt with using appropriate techniques. The robustness of the findings will be assessed and further uncertainties will be addressed by further sensitivity analysis. Except where described below secondary outcomes (e.g. IPOS Neuro, EQ-5D, HADS, ZBI-12) will be analysed in similar fashion to primary outcome. The Wilcoxon (Breslow) test, which is more sensitive to early survival differences as is appropriate in a fast-track or wait list trial design, will be used to test for differences in survival between study arms. Where regression diagnostic checks suggest model distributional assumptions are not met, confidence-intervals and test statistics will be calculated using boot-strap methods.

Tests of homogeneity of treatment effect across the items (symptom profile) of the IPOS Neuro-S8 will be undertaken within the differential-item functioning framework of Item-Response Theory. Bar charts of mean/median data (as deemed appropriate) and box plots showing means and 95% CI for each treatment group at each time point will also be produced. For describing patient and caregiver reported outcomes we will use descriptive analysis to summarise the data by trial arm. We will monitor adverse events. Numbers of deaths in each arm in total and by disease will be reported together with the relative risk and confidence intervals estimated using Cox regression, stratified by disease. An analysis joint with QoL ratings will also be undertaken. We will use latent growth curve model to evaluate how the intervention effects on primary and secondary outcomes change over time.

Cost-effectiveness will be assessed by linking data on service cost differences and two outcome measurements (IPOS Neuro-S8 and ICECAP-A) differences. If post SIPC has significantly lower costs and significantly better outcomes then SIPC will be deemed to be more cost-effective. If costs are significantly higher and outcomes significantly better or if there is uncertainty in these findings then we will use the net benefit approach and cost-effectiveness acceptability curves to assess cost-effectiveness. Cost-utility analysis will be conducted in the same way as the cost-effectiveness analysis but will use QALYs (derived from the EQ-5D-5L) as the outcome measure.

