The MPCT comprises individuals specifically trained in palliative care from (at least) backgrounds in medicine, nursing and psychosocial care or social work. The MPCT has regular multidisciplinary meetings to review patients in their care and is able to visit patients at home in the community. We will ensure that the MPCTs are integrated into local MS, PRDs, and MND care teams to ensure coordination of care. For the purpose of this study, the MPCT will operate a key worker process where a specialist team member will take initial responsibility for a patient referred, although the key worker may change during the course of the intervention. This involves key features of case management, training of health professionals to support self-care ('guided care') and planning levels of specialist input depending on the needs of individuals. The key worker liaises regularly and integrates care with neurologists, nurses, rehabilitation, primary and hospice services to discuss patients of concern. Based on their visits and assessments the key worker generates a problem list with the patient and outlines a proposed action plan, agreed with the patient and family (which is thus individually tailored). This might involve a change in symptom management (e.g. drug change), contact with other services, and/or psychosocial support or counselling during the visit. The key worker reviews and revises, at a multiprofessional team meeting, the problem list, their assessment and the action plan to optimise the management of the patient and caregiver and plan future visits and liaises with other professionals, e.g. to agree medication or service change.

In MPCTs the nurses and allied health professionals do not usually have prescribing powers, they advise regarding medications, although this may change over the time of the project. The palliative care teams all have doctors who can prescribe, but would do so in liaison with the GP and neurologist. If the nurses began to prescribe we would record this, but they would do so in liaison with other professionals.

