### **14.3 Intervention records**

The palliative care team will keep a standardised proforma(s) for each patient (and family). This will record the main activities and services provided to patients, families and other professionals. This will include: for intervention visits who has contact, contact duration, clinical details and severity of main problems using aspects of the staff version of IPOS Neuro (using the standard methods as used in the NIHR C-Change project), any recommended changes to medications, what kind of activities were performed during contact, plan of care and referrals to other services. In addition at each visit, staff will record assessment of phase of illness (stable, unstable, etc) and functional status. A record of contacts outside the intervention visits will also be kept. To ensure fidelity of the SIPC we will undertake quality assurance and observation of activity in the centres throughout the trial.

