## 20. Statistics

### 20.1 Sample Size

Based on the data from our Phase II MS trial, the five centres altogether need to recruit 356 patients. In view of the advanced illness in this patient group we have allowed 20% attrition (phase II trial attrition from death or illness: 3/52) to the primary 12-week outcome, giving 296 patients, or 148 in each arm with both baseline and 12-week outcome data. The correlation between baseline and the 12-week outcome in the pilot study was 0.55. Using generalised linear model to adjust for the baseline score, with two-sided  $\alpha=0.05$  and correlation of 0.40, the study will have 80% power for a medium effect size of 0.30. To allow for heterogeneity across conditions and centres, we used conservative figures (eg. correlation 0.4 rather than 0.55; 20% attrition) to estimate the sample size. For the qualitative study, we estimate a sample size in each study site of seven patients/caregivers, total 35 patients/ caregivers in qualitative sample and six service providers/service commissioners from each site, total of 30 providers/commissioners. For the pilot phase we aim to recruit 15-25 patients/caregivers. The survey of health professionals will be primarily descriptive. It will be sent to a random sample of 200 health professionals, 40 in each area, with a mix of primary and secondary care staff identified as those referring to or interacting with SIPC. We estimate a response rate of 50-60% with 2 reminders giving at least 100 completed questionnaires.

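### SIPC patients share key workers and controls have none, but the primary analysis names no provider term and the 80% power assumes independent patients

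*Protocol*

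**What the plan says.** Section 16.4 of the protocol randomises individual patients 1:1. Section 14.1 states that "the MPCT will operate a key worker process where a specialist team member will take initial responsibility for a patient referred". That person assesses the patient, draws up a tailored plan and coordinates care, although the key worker may change. The intervention manual appended to the protocol (section 2, Standard Care) tells the palliative care teams not to offer specialist palliative care to controls during the first twelve weeks.

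Section 20.2.1 specifies the primary analysis "using generalised linear mixed model with centre as a fixed effect", adjusted for the baseline score and for imbalanced baseline variables, with a test of intervention by centre. No random term is listed.

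Section 20.1 claims that "the study will have 80% power for a medium effect size of 0.30", "with two-sided $\alpha=0.05$ and correlation of 0.40", after attrition "giving 296 patients, or 148 in each arm with both baseline and 12-week outcome data". It adds that "we used conservative figures (eg. correlation 0.4 rather than 0.55; 20% attrition) to estimate the sample size", and gives heterogeneity across conditions and centres as the reason. Providers are not mentioned.

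Section 14.3 requires the team's proforma to record, "for intervention visits who has contact, contact duration" among other items. Manual sections 7 and 8 expect delivery to differ between sites and individual practitioners and set out to learn why.

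**The concern.** At the primary endpoint the design is partially nested: patients in one arm are grouped under providers, and patients in the other are not. If some key workers get better results than others, patients who share one have correlated outcomes, and 148 SIPC patients carry less information than 148 independent patients.

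The provisions in section 20.2.1 do not deal with this:

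- Centre as a fixed effect removes level differences common to both arms. It does not remove key-worker differences within a centre's SIPC arm.
- The intervention-by-centre test compares centres and leaves the standard error of the main effect unchanged.
- The bootstrap is triggered by failed distributional assumptions, not by correlated observations.

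At stake are the confidence interval and error rate of the primary comparison and the accuracy of the power claim. Most secondary outcomes are to be analysed in similar fashion, so the gap carries over to them.

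**Working it through.** **Inputs from protocol section 20.1:** two-sided alpha 0.05; standardised effect 0.30; baseline to 12-week correlation 0.40 (0.55 in the pilot); 148 analysed per arm.

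**Assumed, because the protocol gives neither:** 10 to 30 key workers in all, so 148/30 = 4.9 to 148/10 = 14.8 analysed SIPC patients each; ICC 0.01 to 0.05.

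**Step 1: the stated power.** Residual SD after baseline adjustment = √(1 − 0.40²) = 0.917. Standard error = 0.917 × √(2/148) = 0.1065. Power = Φ(0.30/0.1065 − 1.96) = 80.4%. The same formula needs 147 per arm for 80%, against 148 stated. The claim is therefore reproduced as a baseline-adjusted comparison of independent patients, with no design effect in it.

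**Step 2: clustering in the SIPC arm only.** With m patients per key worker:

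- Design effect in the SIPC arm: DE = 1 + (m − 1) × ICC
- True SE divided by the SE that ignores key workers: r = √((1 + DE)/2)
- Power = Φ(0.30/(0.1065 × r) − 1.96)
- Actual two-sided type I error = 2 × (1 − Φ(1.96/r))

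| Key workers | m | ICC | DE | r | Power | Type I error |
|---|---|---|---|---|---|---|
| 30 | 4.9 | 0.01 | 1.04 | 1.01 | 79.6% | 5.2% |
| 15 | 9.9 | 0.02 | 1.18 | 1.04 | 77.0% | 6.0% |
| 15 | 9.9 | 0.05 | 1.44 | 1.10 | 72.2% | 7.6% |
| 10 | 14.8 | 0.05 | 1.69 | 1.16 | 68.0% | 9.1% |

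Worst row: DE = 1 + 13.8 × 0.05 = 1.69; r = √(2.69/2) = 1.16; SE = 0.1065 × 1.16 = 0.1236; power = Φ(0.30/0.1236 − 1.96) = 68.0%. With ICC = 0, r = 1 and nothing changes.

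**Step 3: the headroom in the cautious correlation.** At 0.55, residual SD = √(1 − 0.55²) = 0.835, SE = 0.835 × √(2/148) = 0.0971, and power without clustering = Φ(0.30/0.0971 − 1.96) = 87.1%. Power stays at 80% while r ≤ 0.30/((1.96 + 0.84) × 0.0971) = 1.10, that is, up to DE of about 1.43. At DE 1.69, SE = 0.0971 × 1.16 = 0.1126 and power is Φ(0.30/0.1126 − 1.96), about 76%. The type I error column does not change, because r does not depend on the correlation with baseline.

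**The case against.** **The random terms may be in the statistical analysis plan.** The protocol calls the model mixed without listing its random terms, and section 26.2 refers to a pre-agreed analysis plan that is not shown. This stands in part. A reader might infer that provider effects have been ruled out; the text shows only that none is named. But the power claim is fixed in the protocol, and no later plan can fit a key-worker term unless the identifier was collected. Manual section 6 lets teams use their own record forms, and its minimum list names no such identifier. The contact form in manual Appendix 2 asks for professional type, and only for contacts outside study visits.

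**The size is assumed.** This stands. A reader might infer that the interval is definitely too narrow, or that power falls as low as 64% with type I error 10.7%. The first holds only if the ICC exceeds zero. The second needs ICC 0.05 and 20 analysed patients per key worker (DE = 1 + 19 × 0.05 = 1.95), or about 148/20 ≈ 7 key workers over five or more centres, and nothing in the protocol supports so few. Nor would SIPC-only clustering arise if SIPC changed nothing for anyone; the inflated error rate concerns a zero average effect with provider effects that vary around it.

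**The conservative correlation already covers it.** For power this is partly right, as step 3 shows, so a true power below 80% is not established. It does nothing for an interval that ignores clustering.

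**The key worker is an imperfect cluster unit.** The key worker may change, later visits may be made by another team member, the whole team reviews the plan, and common training and audit aim to standardise care. Patients are not treated in groups. All of this could make the ICC small, but it does not make it zero. It means that the unit must be defined.

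**Changing the primary model has costs.** Sections 16.4 and 20.2.1 keep the statistician blind, and an identifier held only for SIPC patients would reveal allocation. Clusters would be few, and some SIPC patients may never be assessed. These points stand and argue for a sensitivity analysis rather than a new primary model.

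**Conclusion.** The concern holds in conditional form. The design is partially nested at 12 weeks, section 20.2.1 names no provider term, and the 80% in section 20.1 reproduces only for independent patients. If the key-worker ICC is above zero, the planned standard error is too small. Over the assumed range the effect runs from negligible to material: a true standard error 1% to 16% larger, type I error 5.2% to 9.1%, and power from about 80% down to 68% at correlation 0.40. At the pilot correlation the corresponding power range starts from about 87% without clustering and reaches about 76% at the worst assumed case. The range rests on assumed caseloads and ICCs, equal cluster sizes and a normal approximation. The protocol neither confirms nor rules out a value within it.

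**What to change.** 1. In section 20.2.1, name a sensitivity analysis of the primary effect with a random effect for the key worker who made the first assessment, in the SIPC arm only. Treat controls and SIPC patients who were never assessed as singletons, so that everyone randomised to SIPC stays in that arm. Use a small-sample degrees-of-freedom correction, since the clusters will be few.
2. Record that key worker's identifier for every SIPC patient, as a coded field drawn from the proforma in section 14.3. Hold it apart from the blinded dataset and run this analysis only after the blinded primary analysis is complete.
3. In section 20.1, state that 80% power assumes no key-worker clustering, and give the range above with its assumed ICC and caseload.

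The cost is one extra field, one extra analysis, and possibly a wider interval in that analysis and a less favourable power statement. The primary model, the blinding and the sample size stay as they are.

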### 16.4 Randomisation Procedure / Code Break

Following consent, baseline interview and registration of patient on the MACRO eCRF, the patient will be allocated a unique PIN which will identify them throughout the course of the trial. The individuals will be randomised to one of the trial arms using minimisation method, stratified by center, primary diagnosis (MS, IPD, PSP & MSA, and MND) and cognitive impairment. Randomisation will be done in a 1:1 ratio and will be at the patient level. Randomisation will be performed using an online randomisation system based at King's Clinical Trials Unit (King's CTU), which can be accessed at [www.ctu.co.uk](http://www.ctu.co.uk) by clicking 'randomisation – advanced' on the lower right hand side of the page. The trial coordinator (or someone supervised by the TM) will be notified of the trial arm allocation of the patients and arrange intervention and/or follow-up visits. The research nurses who will conduct the interviews and the trial statistician will be blinded to the trial arm allocation. Overall, we do not expect to need to unblind (code break) to the research nurses or to the trial statistician during the periods of trial and primary analysis. After the primary endpoint of 12 weeks, in a small number of cases research nurses are needed to conduct a qualitative interview with a patient who has received the intervention, where we cannot find another researcher to do this interview, which will effectively unblind the research nurses. We will keep this to a minimum and ensure it is after the primary endpoint of the study.

Any problems with the online randomisation system should be reported to the Trial Manager or the King's CTU at [[contact]](mailto:[contact]) or on [name].

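### The primary model adjusts for whichever baseline variables happen to be imbalanced, so it cannot be written down in advance and will tend to omit two of the three minimisation factors

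*Protocol*

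**What the plan says.** Protocol section 20.2.1 describes the primary analysis as an intention-to-treat "generalised linear mixed model with centre as a fixed effect, adjusting for baseline score of IPOS Neuro-S8" and extends the adjustment to further terms "for variables from the baseline assessment for which treatment-group imbalance is found". It gives no list of candidate variables, no definition or threshold of imbalance, and no statement of the patient set on which imbalance is judged. Most secondary outcomes are to be analysed in the same way.

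Section 16.4 describes allocation: "Randomisation will be done in a 1:1 ratio and will be at the patient level", by minimisation on centre, primary diagnosis (four groups) and cognitive impairment. Of these three factors, only centre is named in the primary model.

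Section 20.1 bases the sample size on adjustment for the baseline score alone, "giving 296 patients, or 148 in each arm with both baseline and 12-week outcome data", and states that "the study will have 80% power for a medium effect size of 0.30".

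**The concern.** Baseline data are collected before randomisation, so among all randomised patients any difference between arms is chance. The value of adjusting for a covariate comes mainly from how well it predicts the outcome, and the rule ignores that. It can admit a variable with no bearing on the week-12 score and pass over a predictive one that happens to be balanced.

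It also sits badly with the trial's own design. Minimisation is used to balance diagnosis and cognitive impairment, so a rule triggered by imbalance will usually leave them out. Yet section 20.1 gives heterogeneity across conditions as a reason for caution in the sample size, and section 20.2.1 stratifies the Cox regression for deaths by disease.

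Because imbalance is not defined, two competent statisticians could fit different primary models to the same data. At stake are the pre-specification of the primary result, some precision, and an interval that matches its nominal coverage.

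**Working it through.** **Inputs from the protocol.** 148 per arm with outcome data, standardised effect 0.30, baseline-outcome correlation 0.40, two-sided alpha 0.05 (section 20.1). The 148 is taken as stated.

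**Assumptions, because the protocol gives no figure.** The number and strength of other covariates and the imbalance threshold. Several values are shown.

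**1. The plan's own figure.** Residual SD after baseline adjustment = √(1 − 0.40²) = 0.9165. Power = Φ(0.30 × √(148/2) / SD − 1.960). Here 0.30 × √74 = 2.581, so 2.581/0.9165 = 2.816 and Φ(0.856) = 80.4%. The stated 80% is reproduced.

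**2. How often the rule acts.** With ten independent candidates tested at p<0.05, at least one is imbalanced by chance with probability 1 − 0.95^10 = 40%. If imbalance means a standardised difference above 0.1, each candidate qualifies with probability P(|Z| > 0.1 × √74 = 0.860) ≈ 0.39, and at least one does with probability 1 − 0.61^10 ≈ 99%. The definition largely decides the model.

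**3. Type I error and standard error under the rule.** Simulation with 148 per arm, correlation 0.40, ten candidates and 8,000 to 15,000 trials per scenario:

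| Predictive covariates among the ten | Selection | Type I error | Power, rule | Power, those covariates always included |
|---|---|---|---|---|
| 3, r = 0.30 each | p<0.05 | 3.8-4.7% | 81-82% | 92% |
| 3, r = 0.30 each | std. difference >0.1 | 3.1-3.2% | 86% | 92% |
| 1, r = 0.50 | p<0.05 | 4.4% | 81% | 92% |
| 3, r = 0.15 each | p<0.05 | 4.5% | 79.6% | 82.7% |
| none | p<0.05 | 5.1% | 80% | 80% |

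Where covariates are predictive, the model's standard error exceeds the true spread of the estimate: 0.106 against 0.101-0.105 in the first row, and 0.101 against 0.092 in the second. Intervals are somewhat too wide and the test is conservative.

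**4. Freedom of definition.** Taking the most favourable of three definitions (p<0.05, p<0.10, standardised difference above 0.1) in the r = 0.30 scenario gives type I error of 5.1%, against 3.1-3.8% for each definition alone.

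**5. What a fixed list could gain.** The list proposed below adds two covariates. If together they explain a further share R² of outcome variance, residual SD = √(1 − 0.16 − R²):

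- 2% each: SD = √0.80 = 0.894; 2.581/0.894 = 2.885; power = Φ(0.925) = 82%.
- 5% each: SD = √0.74 = 0.860; 2.581/0.860 = 3.000; power = Φ(1.040) = 85%.
- 10% each: SD = √0.64 = 0.800; 2.581/0.800 = 3.226; power = Φ(1.266) = 89.7%.

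Simulation of the imbalance rule with the same two covariates gives about 80-81% throughout. The gain is about 2, 4 or 8 points.

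**The case against.** Several points on the other side stand.

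- The covariate whose predictive strength is documented, the baseline score, is always in the model, and so is centre. No document shows another strong predictor.
- Selection uses baseline data and allocation, not the week-12 outcome, and section 20.2.1 keeps the trial statistician blind to assignment. That limits deliberate choice. It does not fix the model beforehand, since imbalance is visible between coded arms.
- A statistical analysis plan may define candidates and a threshold. Even so, under the protocol's clause the covariates would still depend on the comparison of the arms. This is a rule that the protocol states, not a detail that it leaves open.
- The protocol expects attrition and data missing not at random, so differences among the patients analysed need not be pure chance. A chance-imbalance rule is not a remedy for that either.

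A reader might infer that the rule inflates false positives. The calculations do not support this: applied mechanically it is conservative, and even picking among three definitions only brings the level back to about 5%. A reader might also infer that power falls short of plan. It does not, because the planned 80% assumes baseline adjustment only. Finally, the gap of roughly 81% against 92% in the table needs covariates that explain about 25% of outcome variance, and diagnosis and cognitive impairment are not shown to do so.

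**Conclusion.** The point holds in a limited form. The protocol places a data-driven covariate rule inside the primary analysis. The primary model therefore cannot be stated before the arms are compared, and the rule tends to exclude two of the three minimisation factors. With selection at p<0.05, type I error is about 4-5% and power about 80-81%, so neither the 5% level nor the planned power is threatened. The cost is a forgone gain of about 2 to 8 power points if two added covariates explain 2% to 10% of variance each, and essentially nothing if they predict nothing. Those strengths, the number of candidates and the thresholds are assumptions. The change should be made because it is free and removes an avoidable dispute over covariate choice, not because the result would otherwise be invalid.

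**What to change.** In section 20.2.1, replace the imbalance clause with a fixed covariate list: baseline IPOS Neuro-S8, centre, primary diagnosis and cognitive impairment. Use the same list for the secondary outcomes that follow the primary method, with each outcome's own baseline value in place of the IPOS Neuro-S8 score. Present baseline tables by arm descriptively, without using them to choose covariates. If an imbalance-adjusted model is wanted, label it a sensitivity analysis and define imbalance, the candidate variables and the patient set in advance.

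The cost is one sentence in the protocol and a matching entry in the statistical analysis plan. Diagnosis and cognitive impairment are already recorded for minimisation, so no new data or patients are needed. The change should be made before anyone compares the arms.

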**Randomisation with minimization (with random element) stratified by: centre, disease and cognitive impairment**

### Standard Care (Control/Delayed intervention arm, n=178)

After randomisation, patients will continue their usual services and treatments. After the second follow-up interview (approximately 12 weeks), they will be offered the SIPC and followed up to the end of the study.

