| Sample Size:                     | 356, 178 in each arm (short-term integrated palliative care vs standard care)                                                                                                                                                                                                                                                                                                                                                                                                                                                                                                                                                                                                                                                                                                                                                                                                                                                                                                                                                                                                                                                                                                                                                                                                                                                                                                                                                                                                                                                                                                                                                                                                                                                                                                                                                                                                                             |

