## **16.6 Expected Duration of Trial**

The trial will run for 40 months, which includes trial set up, recruitment and analysis of data. Patients will receive their intervention for approximately 6-8 weeks and will be followed up for 24-26 weeks (from start of trial, not necessary start of intervention). End of trial is defined as the last patient's last study visit.

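### The survival test names no strata although allocation is minimised on diagnosis and the Cox model for deaths is stratified by it, so the test is conservative if death risk differs between diagnoses

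*Protocol*

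**What the plan says.** Section 20.2.1 of the protocol describes two analyses of death.

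- **A test.** The Wilcoxon (Breslow) test "will be used to test for differences in survival between study arms". It was chosen as a test "which is more sensitive to early survival differences as is appropriate in a fast-track or wait list trial design". No strata or covariates are named.
- **An estimate.** In the next paragraph, numbers of deaths are reported with "relative risk and confidence intervals estimated using Cox regression, stratified by disease".

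On allocation, section 16.4 says patients are randomised by minimisation "stratified by center, primary diagnosis (MS, IPD, PSP & MSA, and MND) and cognitive impairment". The trial flowchart agrees: "Randomisation with minimization (with random element) stratified by: centre, disease and cognitive impairment". The Cox sentence does not list the levels of disease. I take them to be the four diagnosis groups of section 16.4.

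**The concern.** Minimisation keeps the arms close to equal within each diagnosis. If diagnosis also predicts death, the difference between arms varies less by chance than it would under simple randomisation. A test without strata still uses the larger variance, so it rejects too rarely when there is no effect and gives away some power when there is one.

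The protocol itself treats diagnosis as relevant to death: it stratifies the Cox model by it, and sections 19.1 and 19.2 monitor deaths by disease. Eligibility runs from motor neurone disease at any stage to idiopathic Parkinson's disease at Hoehn and Yahr stages 4-5, so equal risk across groups is unlikely.

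A conservative test is safe against a false claim of longer survival. It is less comfortable for safety, because it also lowers the chance of seeing excess deaths in either arm.

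**Working it through.** **No figure to reproduce.** The protocol states no event count, power or error rate for survival. Its sample-size calculation concerns the 12-week symptom score.

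**Inputs from the protocol.** 356 patients, allocated 1:1 (Synopsis and section 16.4); minimisation on centre, diagnosis and cognitive impairment, with a random element (flowchart and section 16.4); patients "will be followed up for 24-26 weeks" (section 16.6; 24 weeks used).

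**Assumptions.** These are 24-week death risks by diagnosis, in the order MS, IPD, PSP/MSA, MND, and the diagnosis mix. Mix A is 35/30/15/20% (balanced 1:1 within diagnosis). Mix B is 25/40/20/15% (minimised with a biased coin of 0.8). Survival is exponential, the hazard ratio is constant over 24 weeks, and the test is two-sided at 5%. The only attrition figure in the protocol is 3/52, for death or illness combined in MS, so it cannot supply these rates.

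**Test statistics.** At the j-th death, let n_j be the number at risk, p_j the share of them in the intervention arm, and x_j = 1 if the death is in that arm. Then U = Σ w_j (x_j − p_j), V = Σ w_j² p_j(1 − p_j), and the test rejects if U²/V > 3.84.

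- Breslow, no strata: w_j = n_j over all patients.
- Plain stratified Breslow: U and V are summed over diagnoses, with w_j = n_j within the diagnosis.
- Scaled weights: as above, with w_j = n_j / N_s, where N_s is the size of the diagnosis group. With no censoring before 24 weeks this ratio is the within-group Kaplan-Meier estimate just before the death, which is the Peto-Prentice type of weight.

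**Type I error (nominal 5%; Monte Carlo standard error about 0.3 points; ranges are over separate runs).**

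| Assumed risks, mix | No strata | Stratified by diagnosis |
|---|---|---|
| 9% in every group, B | 5.2% | 5.1% |
| 2/3/5/12%, B | 4.7% | 5.0% |
| 2/4/8/20%, A | 4.3-4.5% | 5.1-5.3% |
| 3/5/10/25%, B | 3.9-4.2% | 4.6-4.7% |
| 3/6/12/35%, A | 3.3-3.5% | 4.8-5.2% |
| 4/8/20/45%, B | 2.9-3.3% | 4.7-5.2% |

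From 2/4/8/20% to 4/8/20/45%, the test without strata runs at about 3 to 4.6%. Scaled weights gave 4.6% (3/5/10/25%, B) and 5.0% (4/8/20/45%, B).

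**Power at hazard ratio 0.5.**

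| Assumed risks, mix | No strata | Plain stratified Breslow | Scaled weights |
|---|---|---|---|
| 2/4/8/20%, A | 29.6% | 29.3% | 31.5% |
| 3/6/12/35%, A | 43.1% | 43.6% | 47.4% |
| 2/4/8/20%, B | 27.1% | 24.7% | – |
| 3/5/10/25%, B | 34.7% | 31.6% | 36.4% |
| 4/8/20/45%, B | 52.8-53.7% | 49.9% | 58.1% |

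Scaled weights gain 31.5 − 29.6 = 1.9, 47.4 − 43.1 = 4.3, 36.4 − 34.7 = 1.7 and 58.1 − 52.8 = 5.3 points, so about 1.5 to 5.5. Plain stratification changes little under mix A (−0.3 and +0.5). Under mix B it loses 27.1 − 24.7 = 2.4, 34.7 − 31.6 = 3.1 and up to 53.7 − 49.9 = 3.8 points.

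**Why plain stratification loses power.** Raw risk-set counts favour large groups. Under mix B, IPD has 0.40 × 356 = 142 patients and MND 0.15 × 356 = 53. An early IPD death therefore counts 142/53 = 2.7 times an early MND death. At risks of 4/8/20/45%, however, without an effect IPD contributes about 142 × 0.08 = 11 deaths and MND about 53 × 0.45 = 24. Scaling within stratum removes this.

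**Test against interval.** At hazard ratio 0.5 under mix B, the Breslow test without strata and the score test of the stratified Cox model reached different verdicts at 5% in 2.9% of trials (3/5/10/25%) and 6.6% (4/8/20/45%). With equal risks they still differed in 1.1%.

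**The case against.** **Silence is not exclusion.** The protocol does not rule strata out, section 26.2 promises a pre-agreed analysis plan, and strata for one secondary test often belong there. That stands as a limit on the point: the analysis plan may already settle it. But section 20.2.1 names both the test and the model and gives strata to only one of them, so the text as written leads to a test that omits an allocation factor.

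**The two analyses have different purposes.** The test sits with the secondary outcomes and the Cox estimate with adverse events, and the early weighting is a reasoned choice for a design in which the control arm is offered the service after 12 weeks. This is fair. A reader might infer that the p-value and the interval contradict each other, or that stratifying would make them come from one model. The documents do not support either. The protocol never pairs them, and after stratification they would still weight deaths differently, because the Cox score test is the log-rank test.

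**The obvious remedy has a cost.** A reader might also infer that adding strata to the Breslow test is free. The power figures show otherwise, so the weights matter as well as the strata.

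**The size is assumed.** That is correct. The protocol gives neither death rates by diagnosis nor a diagnosis mix, and in the milder scenarios the shortfall is only about half a point to one point.

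**Conclusion.** The point holds at modest strength. If death risk differs between diagnoses, the survival test as written is conservative: about 3 to 4.6% type I error against 5% over assumed risks from 2/4/8/20% to 4/8/20/45%. If risks are similar, nothing is lost. The direction follows from balancing on a prognostic factor and then leaving it out; the size rests wholly on the assumed risks and mix. The power comparison also assumes a constant hazard ratio of 0.5 over 24 weeks, although the control arm is offered the service after 12.

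The protocol's preference for weighting early deaths is not at fault, and no survival claim is invalidated: survival is secondary, no power is claimed for it, and the error is on the cautious side. Calling the Cox estimate a relative risk is a matter of label. Because it stands beside numbers of deaths, a reader might take it for a ratio of death proportions, but the model is named and its estimate is a hazard ratio.

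**What to change.** In section 20.2.1, or in the analysis plan if that is where the detail is fixed:

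1. Stratify the early-weighted survival test by the same diagnosis groups as the Cox model, and list them (MS, IPD, PSP and MSA, MND, as in section 16.4).
2. Use weights scaled within stratum, as in a stratified Peto-Prentice type of Wilcoxon test, rather than raw Breslow risk-set counts. This keeps the stated emphasis on early deaths.
3. State that the p-value comes from this test and the interval from the stratified Cox model, and that the two can differ because they weight deaths differently.
4. Call the Cox estimate a hazard ratio.

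The cost is a few sentences and a slightly less standard weighting to program. No new data are needed, because diagnosis is already used at randomisation. The change should be made before survival is compared by arm.
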